## Abstract

**Background:**

Extreme heat exposure — defined as sustained ambient temperatures exceeding local thresholds — has been associated with several adverse pregnancy outcomes, including preterm birth, stillbirth, gestational diabetes and small for gestational age. However, the mechanisms linking environmental heat to these outcomes, and the biological markers that signify individual vulnerability, are not well understood. We present the protocol for a prospective cohort study within the Heat in Pregnancy-India consortium (HiP-India). This study aims to characterise the physiological and pathophysiological responses of the mother, placenta, and fetus to varying levels of temperature, humidity, and air pollution exposure, and to identify the critical windows and mechanisms of heat-related risk during pregnancy.

**Methods:**

600 women with singleton pregnancies, with confirmed gestational age by ultrasound between 11–14 weeks, will be recruited prospectively from three distinct climate zones in India: Gurugram, Delhi NCR ‘semi-arid’; Bilaspur, Chhattisgarh ‘humid sub-tropical and tropical wet and dry’; and Puducherry ‘tropical wet and dry’. Each participant will have their level of exposure to heat, humidity and air pollution measured for 24 hours each trimester in their home and/or workplace using individual and area monitoring devices. Perceived heat stress will be captured using a modified HOTHAPS questionnaire, while physiological heat strain will be measured through urinary specific gravity, core body temperature, heart rate and blood pressure. Within 48 hours of environmental monitoring, maternal haemodynamic parameters will be assessed non-invasively. Fetal ultrasound will be performed to evaluate growth and fetal-placental blood flow, and maternal blood samples collected to evaluate circulating biomarkers of placental function and stress. Cardiotocography will be conducted in the third trimester only. Delivery outcomes for both mothers and neonates will be extracted from hospital records and interviews. In a subset of 100 women, markers of lactation physiology will be recorded during the first 2 weeks after delivery.

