### Sample size

This exploratory study will be powered primarily on multiple physiological and biochemical outcomes, rather than on clinical endpoints, many of which currently lack sufficient preliminary data to enable formal power calculations at the 5% significance level.

Primary outcomes:

Physiological and biochemical measures include maternal core body temperature, urine specific gravity, maternal cardiac output (USCOM), heart rate variability, and angiogenic ratio (sFlt-1/PlGF). Clinical outcomes include preterm birth (<37 weeks of gestation) and birth weight (grams).

Secondary outcomes:

Secondary endpoints comprise gestational age (weeks), small for gestational age (SGA), stillbirth, and additional placental and fetal biomarkers.

A total of 700 pregnant women will be enrolled to account for an anticipated attrition rate of approximately 15%, yielding an expected final sample of about 600 mother–baby dyads with complete follow-up. The majority of outcomes are continuous variables, which—following transformation to approximate normality, if required—will provide 80% statistical power at a two-sided significance level of α = 0.05 to detect a minimum difference of 0.23 standard deviations between high versus low heat exposure groups. This detectable effect size lies well within accepted thresholds for clinical relevance.

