## Ethics approval and study registration

The study has received ethics approval from the following independent institutional ethics committees:

1. Translational Health Science and Technology, Institute, Faridabad (THS 1.8.1/(171)2. Gurugram Civil Hospital (GCH/EC/2021/1826/8.12.2023/28.1)3. Chhattisgarh Institute of Medical Sciences, Bilaspur (327/C.I.M.S/I.E.C/2024)4. Pondicherry Institute of Medical Sciences, Puducherry (RC/2024/08)5. The George Institute for Global Health, India (Project Number 31/2023)6. Sri Ramachandra Institute of Higher Education and Research (IEC/24/MAR/185/07)

Any important protocol modifications (e.g., changes in eligibility criteria, outcomes, or data collection methods) will be communicated to relevant parties, including the institutional ethics committee, trial registry (if registered), and study collaborators. Updated versions of the protocol will be archived and shared through the selected data repository and included in any subsequent publications.

Based on our experience with the ongoing large hospital-based pregnancy cohort at Gurugram Civil Hospital, India (GARBH-Ini)
^
7
^, we anticipate an overall loss to follow-up of 10–15% (study completion rate 85–90%).

Mitigation measures include:

• verifying home addresses at enrolment;

• maintaining regular contact via phone/SMS/WhatsApp;

• leveraging a field worker network for tracing and counselling;

• providing transport support or arranging home visits when hospital follow-up is not feasible.

Additional retention strategies include reimbursements for time/travel, provision of pregnancy health education materials, and facilitation of clinical care at study sites. To ensure adequate power, we will over-enrol by 15–20% to compensate for anticipated losses.

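### The abstract, Table 1 and structured summary give 600 as the number of women, but the sample-size section enrols 700 so that about 600 complete

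*Protocol article*

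**What the plan says.** Four places in the protocol article give the size of the cohort.

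- **Abstract, Methods:** "600 women with singleton pregnancies, with confirmed gestational age by ultrasound between 11–14 weeks, will be recruited prospectively from three distinct climate zones".
- **Table 1 (Biospecimen and data collection methods):** N=600 at 11–14 weeks, 18–22 weeks, 30–34 weeks and birth, with 100 for the lactation substudy.
- **Structured summary:** a target sample size of 600, with 300 in the summer group and 300 in the winter group. These groups are defined by season of recruitment.
- **Sample size:** "A total of 700 pregnant women will be enrolled to account for an anticipated attrition rate of approximately 15" per cent, "yielding an expected final sample of about 600 mother–baby dyads with complete follow-up". The same paragraph says this number "will provide 80% statistical power at a two-sided significance level of α = 0.05" for a difference of 0.23 SD between high and low heat exposure.

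The section Ethics approval and study registration adds that 10–15% loss to follow-up is expected and that "we will over-enrol by 15–20% to compensate for anticipated losses".

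**The concern.** In the abstract 600 is the number of women who enter. In the Sample size section it is the number who remain. Both cannot be true at the attrition the article expects. If 700 enrol, the first visit cannot have N=600. If 600 enrol, about 600 complete dyads cannot result.

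The power statement rests on the number analysed, so a reader needs to know which figure is the intake. The Recruitment section ties screening and outreach to reaching the target sample size, and the only number in the article carrying that label is the 600 in the structured summary. At stake is whether the study that is run has the 80% power claimed for it.

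**Working it through.** **Inputs**

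- Detectable difference d = 0.23 SD, power 80%, two-sided alpha 0.05 (Sample size).
- Enrolment of 700 (Sample size) or 600 (abstract).
- Loss of about 15% (Sample size), or 10–15% (Ethics approval and study registration).
- Over-enrolment of 15–20% (same ethics section).
- Assumption: equal high- and low-exposure groups. The article gives a 300/300 split only for season of recruitment and states no ratio for the exposure contrast.

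**Step 1. Reproduce the plan's figure.** The number per group is 2 × (1.96 + 0.84)² / d². With d = 0.23 this rounds up to 297 per group, or 594 in total. With 300 per group, power is Φ(0.23 × √(300/2) − 1.96) = 80.4%. So 600 works as the number analysed, and the 0.23 SD reproduces.

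**Step 2. Check 700 enrolled.** 700 × (1 − 0.15) = 595, which fits the description of about 600. Power at 0.23 SD is 80.1%. Working backwards, 600 / 0.85 = 706 and 600 / 0.90 = 667, so 700 is a reasonable rounding.

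**Step 3. Take 600 as the number recruited.** Detectable difference at 80% power is (1.96 + 0.84) × √(4/N), where N is the number analysed.

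| Enrolled | Loss | Left | Power at 0.23 SD | Detectable difference at 80% power |
|---|---|---|---|---|
| 700 | 15% | 595 | 80.1% | 0.230 SD |
| 600 | 10% | 540 | 76.2% | 0.241 SD |
| 600 | 15% | 510 | 73.8% | 0.248 SD |

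**Step 4. Check the over-enrolment range against 700.** 700/600 − 1 = 16.7%, which lies inside 15–20%. At the corners of the two ranges:

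- 15% over-enrolment (690): 621 left at 10% loss, 586.5 at 15% loss.
- 20% over-enrolment (720): 648 left at 10% loss, 612 at 15% loss.

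Only the combination of lowest over-enrolment and highest loss falls below 600. The shortfall there is 2.25%, and power is 79.5%.

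**The case against.** The strongest reply is that only the abstract says outright that 600 are recruited. The target in the structured summary can be read as the analysable number. The unchanging N=600 in Table 1 cannot be real attendance at each visit when losses are expected, so it may simply show planned completers. Two sections of the body commit to over-enrolment, and site staff work from the protocol and operating procedures, not from an abstract.

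Much of this is fair, and it keeps the point small. It does not remove the contradiction. An abstract may leave out detail, but this one gives a different number for the same act of recruiting. Table 1 puts 600 at the first visit, where attrition has not yet acted. The summary's seasonal groups are defined by when women are recruited, so 600 reads more naturally there as an intake figure.

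The size of the effect is also open to challenge. The study calls itself exploratory, and its core analysis is mixed-effects modelling of repeated measures, so a two-group calculation is only a guide. That stands, but it is the calculation on which the article rests its own 80%.

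A reader might go further and infer that the over-enrolment commitment is itself too small. The documents do not support this: the stated range is 15–20%, 700 falls within it, and the one corner below 600 costs half a percentage point of power. A reader might also infer that sites will stop recruiting about 100 women early. Nothing in the article shows that they would, and the registry record is not at hand.

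**Conclusion.** The contradiction is real and is one of wording. The arithmetic in the Sample size section is sound: 700 enrolled leaves 595 and 80.1% power at 0.23 SD. What conflicts with it is the 600 recruited in the abstract, the 600 at the first visit in Table 1 and, on its natural reading, the 600 target in the structured summary.

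If 600 were the actual intake, power would be about 74–76% instead of 80%, a loss of about 4 to 6 percentage points, and the detectable difference would rise by about 0.01–0.02 SD. This rests on the stated 10–15% loss and on equal exposure groups. The second assumption is not stated, but it is the one under which the plan's 0.23 SD reproduces. The effect is modest, but the enrolment figure carries the power claim and should be the same throughout.

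**What to change.** If 700 is the enrolment target, say so in the abstract, in the 11–14 week column of Table 1 and in the structured summary, and label 600 as the expected number completing. The later columns of Table 1 can then be marked as expected completers. The 300/300 seasonal split should be labelled the same way; if an equal split is kept at enrolment, it becomes 700/2 = 350 per season. The 15–20% over-enrolment statement agrees with 700 and needs no change.

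If 600 is the true enrolment cap, restate the detectable difference in the Sample size section as about 0.24–0.25 SD at 80% power, and withdraw the 700 and the over-enrolment commitment, which would no longer apply.

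The first route costs only wording and changes neither design nor analysis. The second also means accepting a slightly larger detectable difference.

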**Ethics and dissemination of results:**

All necessary ethical approvals from relevant committees at participating institutions have been obtained. Written informed consent will be obtained from all participants. The findings from this study are expected to inform climate adaptation strategies and emergency response policies to protect pregnant populations from the impacts of extreme heat, both within India and in other similarly affected regions globally. Results are aimed for journal publication, communicate findings to participants in plain language, disseminating information at conferences and events of similar nature.

## Background

Pregnant women residing in tropical climates, particularly from low- and middle-income countries (LMICs) are some of the most vulnerable to the effects of climate change
^
1
^. Exposure to extreme heat, defined as ambient temperatures exceeding locally adapted thresholds, has been linked to a range of adverse pregnancy outcomes, including preterm birth, stillbirth, gestational diabetes, small for gestational age, and preeclampsia
^
2,
3
^. These adverse outcomes contribute to infant and under-5 mortality and morbidity, exacerbating existing health inequities in LMIC settings.

India has reported a marked rise in the intensity, frequency, and duration of heatwaves over the last half century
^
4
^. The years 2022 and 2024 were documented to be the hottest since 1901, as per the records of the Indian Meteorological Department (IMD). Recent studies have revealed a spatiotemporal shift in heat wave events over India, resulting in the identification of three distinct heat wave hotspots in the country: Northwestern, Central, and South-Central India
^
4,
5
^. Rekha
*et al.* have documented the heightened risk of mothers working in high-temperature settings in India with adverse pregnancy outcomes
^
6
^. However, the biological mechanisms that mediate these effects — including maternal thermoregulation, placental perfusion, and fetal development — remain poorly characterised.

The Heat in Pregnancy-India (HiP-India) consortium aims to understand how extreme heat exposure affects maternal, placental, fetal, and lactation physiology, and how these changes result in adverse pregnancy outcomes, to help identify who is most vulnerable during extreme heat events, and future interventions to protect pregnant women and babies. The consortium is adopting an ambispective study design, utilising both retrospective data (from the GARBH-Ini cohort
^
7
^, and a large nationally representative, anonymised database of fetal heart rate monitoring), and prospective data from a novel cohort of women recruited from three different climate zones in India. Parallelly, the study will assess women’s experiences and protective mechanisms against extreme heat in the three sites, as part of the qualitative and community engagement part of the research. The retrospective and qualitative branch of the study are not specified in this paper. This manuscript presents the profile and methodology of the prospective cohort arm.

## Objectives

### Study hypothesis

It is hypothesised that environmental heat exposure during pregnancy adversely affects maternal, placental, fetal, and lactational physiology through disruptions in haemodynamics, placental function, and thermoregulatory mechanisms. These physiological alterations may lead to measurable changes in biomarkers, fetal growth trajectories, and birth outcomes. Refer to
Figure 1.

**Figure 1. f1:**
[figure not shown]
Overall HiP-India Study overview and prospective cohort study highlighted under the red dashed circle. *WP= Work Package. The prospective cohort described in this paper encompasses WP 2a–e*.

### Primary objective

To determine the effect of exposure to environmental heat, humidity, and air pollution on maternal, fetal, and placental biological and physiological parameters during pregnancy and identify putative pathways leading to adverse pregnancy outcomes in Indian women.

### Secondary objectives

1. To identify biomarkers and clinical factors associated with heat exposure and adverse pregnancy outcomes.

2. To explore the mechanistic pathways linking environmental heat exposure to adverse pregnancy outcomes.

3. To identify potential confounders and effect modifiers of the associations

## Study design

This will be a multicentre prospective cohort study enrolling pregnant women at 11–14 weeks of gestation and following them up until two weeks after birth. The study aims to capture detailed environmental, clinical, physiological, and biochemical data across key gestational windows, enabling a comprehensive assessment of the maternal and fetal response to heat exposure over time.

### Study setting

The three study locations were selected to represent distinct climate zones across India, each with unique environmental exposures relevant to maternal and child health. Gurugram is located within the Delhi National Capital Region (NCR) and experiences a
**semi-arid climate**, characterised by extreme temperature variations, with scorching summers, cold winters, and limited rainfall, resulting in prolonged dry spells and frequent heatwaves. Chhattisgarh represents a
**humid subtropical to tropical wet and dry climate**, marked by high humidity, hot summers, and a well-defined monsoon season, creating conditions of alternating intense heat and moisture. Puducherry, situated along the southeastern coast, exemplifies a
**tropical wet and dry climate**, with persistently high temperatures, elevated humidity, and pronounced monsoon periods, particularly during the northeast monsoon. These diverse climatic conditions provide a natural contrast in thermal environments, enabling the study to capture a range of heat exposures and their differential impacts on pregnancy-related outcomes across varying ecological contexts.

**Site 1: Gurugram**

Gurugram Civil Hospital (GCH) is a secondary-care hospital that serves a rural and semi-urban population of 1.5 million people in the Gurugram district in Haryana, Northern India. GCH is a referral hub for 22 primary health centres and every month, an average of 900 women attend the antenatal clinics, and 500 infants are delivered in the hospital. Safdarjung Hospital (SJH) is the referral institution for GCH for high-risk pregnancies. The enrolled participants are provided with standard care by the physicians at both GCH and SJH.

**Site 2: Puducherry**

Pondicherry Institute of Medical Sciences (PIMS) is a multi-speciality hospital and teaching Institute in the Union Territory of Puducherry, South India. The hospital is funded by the Madras Medical Mission, a charitable organisation that offers healthcare services at subsidised rates. PIMS laboratory is National Accreditation Board for Testing and Calibration Laboratories (NABL) accredited in medical testing for Clinical Biochemistry, Clinical Pathology, Haematology, Histopathology, Microbiology & others. PIMS has established the Demographic Developmental Environmental Surveillance Site (DDESS) funded by the Department of Biotechnology, Government of India which consists of a population of over 56,000 across 24 villages in the districts of Pondicherry and Tamil Nadu. Approximately 90 women attend the antenatal clinic daily with 100 deliveries conducted monthly. Study participants will be recruited from these villages through community-based screening.

**Site 3: Chhattisgarh**

Chhattisgarh Institute of Medical Sciences is a multispecialty hospital and the second largest public medical college in Bilaspur in Chhattisgarh. The department of Obstetrics and Gynaecology runs a busy clinical service with 70 to 80 women attending each antenatal outpatient clinic, daily admissions of 25 to 30 pregnant women and approximately 600 deliveries each month. The department also draws a large number of emergency referrals from rural areas of the district as well as neighbouring districts. The department of radiodiagnosis performs 15 ultrasound scans per day, with other cases performed in the private sector. Diagnostic services in imaging, biochemistry, pathology, and microbiology are available on-site, with approximately 15 antenatal ultrasound scans performed daily. Study participants will be recruited from the antenatal outpatient clinics at CIMS.

### Inclusion criteria

Pregnant women fulfilling the following inclusion criteria will be considered eligible if they have:

Confirmed singleton pregnancyGestational age between 11 and 13+6 weeks at the time of recruitment, determined by ultrasound-based crown-rump length measurementRecruitment during predefined seasonal windows corresponding to site-specific climatic extremes:Gurugram: warm season (April–July) and cool season (November–February)Puducherry: warm season (March–June) and cool season (November–February)Chhattisgarh: warm season (March–June) and cool season (November–February);Elevated risk of heat exposure based on occupational or household factors, including employment in agriculture, construction, factories, or street vending; residence in poorly ventilated homes, homes with metal roofing, or use of traditional biomass stoves (chulhas)Willingness and ability to provide informed consent and participate in all study assessments, including home- and workplace-based environmental monitoring throughout pregnancy

### Exclusion criteria

Pregnant women will be excluded if they:

Are aged below 18 yearsRegular use of fixed air conditioning at home or workplace (use of fans or coolers is permitted)
Have an underlying severe medical condition (e.g. end-stage renal failure, cardiac disease, cancer, severe mental health problems, severe anaemia, severe endocrine and metabolic disorders)Intention to relocate from the study area prior to deliveryEvidence of active vaginal bleeding at the time of recruitmentSuspected chromosomal or structural fetal anomalies incompatible with life, identified on first trimester ultrasound

### Recruitment

Potential participants will be identified by clinic staff deployed at each hospital antenatal care centre and community health workers from surrounding villages. Recruitment will be supported by routine screening during antenatal visits, community outreach, and engagement with local health workers to ensure adequate enrollment and timely identification of eligible women to meet the target sample size. The project staff will approach potential participants and provide verbal information about the project, along with the participant information sheet. To supplement the information about the project, the team will provide pamphlets at each site, briefly describing its aims and overall outline, including details about the home visits. For those with low literacy or a preference for oral or visual information, a short video will be shown to convey the same information in the local language, which can be viewed on the project member’s tablet computer. The participant information sheet will describe the project, outline the activities involved if they participate, and detail any potential risks and benefits. Participation in the study will not influence clinical care delivery in each site; however, if clinical conditions are suspected during any of the study assessments, women will be referred to the local obstetric team for review. Participants will have an opportunity to ask questions to the study team members.

An orientation to the study will also be conducted for the landlords for the participants who stay in rented accommodations to explain the nature of the environmental assessments. 

For women who are willing to participate, a dating ultrasound will be arranged within the next 7 days to confirm her pregnancy is (i) viable and the inclusion criteria as mentioned above. If the dating ultrasound report indicates a gestation period of less than 10 weeks, the participant will be invited back for another scan within the enrolment window period of 11- 13+6 weeks of gestation. The participant will be asked to provide written informed consent to participate in the study after confirmation of the inclusion criteria. It will be made clear that she can withdraw her consent at any time during the study, with the option also to remove any data collected up to that point if she wishes. As all participants at the GCH site will also be enrolled in the GARBH-Ini Cohort
^
7
^, participation in this study will require a separate consent.

The informed consent will include participation for home/workplace climate and heat strain assessments, ultrasound scans conducted at each trimester, maternal haemodynamic assessments, blood tests taken in each trimester, CTG in the third trimester, and for outcomes at birth to be extracted from her medical records and those of her baby either at site (if delivery done at site) or from after delivery through a planned home visit. A subset of women at the GCH site will also be consented for lactation samples and an additional blood sample to measure serum prolactin levels.

